### Reporting of adverse events

All Adverse Events must be recorded in the case report form, defining relationship to study medication and severity.

**As soon as the Investigator is aware of a potential Serious Adverse Event (SAE), he/she should contact by phone, fax or e-mail, and in any case no later than 24 hours after the knowledge of such a case**.

At the time of the call, the Investigator must provide as a minimum requirement, the patient number, birth date, nature of the SAE, and a preliminary assessment of causality. The Investigator should follow-up the initial notification of the potential SAE by faxing a copy of the SAE reporting form to **Renal Section, Department of Transplant Medicine**

Follow-up information on an existing SAE that is fatal or life-threatening should be reported by the Investigator **Renal Section, Department of Transplant Medicine**  within 5 days after the initial report. Where appropriate, hospitalisation or autopsy reports should be made available. All Serious Adverse Events will be followed up until resolution (i.e., asymptomatic, stabilisation or death).

## Serious Adverse Reactions and Unexpected Adverse Reactions

### Definitions

Adverse Reaction:

All noxious and unintended responses to a medicinal product related to any dose should be considered adverse drug reactions.

The phrase "responses to a medicinal product" means that a causal relationship between a medicinal product and an adverse event is at least a reasonable possibility, i.e., the relationship cannot be ruled out.

For marketed medicinal products, an adverse reaction is a response to a drug which is noxious and unintended and which occurs at doses normally used in man for prophylaxis, diagnosis, or therapy of disease or for modification of physiological function.

Unexpected Adverse Reaction:

An adverse reaction, the nature or severity of which is not consistent with the applicable product information (e.g. product information sheet such as the Summary of Products Characteristics (SPC)).

Suspected Unexpected Serious Adverse Reaction (SUSAR):

Any serious adverse reaction that might be related to the study medication and are unexpected according to the definition above.

### Reporting of suspected unexpected serious adverse reactions by CRO

Suspected unexpected serious adverse reactions (SUSARs) will be reported **Renal Section, Department of Transplant Medicine** according to appropriate Competent Authority and Ethics Committee requirements. CRO will report SUSARs to Investigators <preferably twice yearly, should be adapted to the type of trial according to ICH Good Clinical Practice and to local regulations. SUSAR reporting to the Competent Authorities and Ethics Committees will be performed according to local regulations. The Competent Authorities will be notified of all SUSARs through the Eudravigilance database.

Fatal and life-threatening SUSARs should be reported by **Renal Section, Department of Transplant Medicine** as soon as possible to the Competent Authorities and Ethics Committees according to local regulations, and in any case no later than seven calendar days, after knowledge by CRO of such a case. Relevant follow-up information on the case will be subsequently communicated within an additional eight days. All other SUSARs shall be reported to the Competent Authorities concerned and to the Ethics Committee concerned according to local regulations as soon as possible but within a maximum of fifteen days of first knowledge by **Renal Section, Department of Transplant Medicine.**

# STATISTICAL METHODOLOGY AND DATA MANAGEMENT

## Study Design

This clinical trial employs a Randomized, open control design. Randomisation is used to minimise assignment bias and to increase the likelihood that known and unknown patient attributes. Estimation of Sample Size:

Assuming a type 1 error of 5% and at type II error of 20 %, with a clinically relevant difference in 5.2 mg/mmol from a baseline value of 15.0 + 10 mg/mmol the estimated number of patients in each arm should be 30, assuming a correlation between start and end value of 0.5. In case of early drop-outs additional patients can be included to ensure that a total number of 70 patients will be randomized.

## Randomisation

The randomisation scheme (in a 1.1 ratio) will be generated by CRO using a computerised procedure. A complete randomisation list containing details of all patient numbers and study group will be stored as essential documentation in the Trial Master File and at the study site (open study).

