# TREATMENT PROCEDURES

## Overall Study Design

The study is to be performed as a randomized open intervention study. Patient eligibility for the trial will be assessed around 4 weeks after transplantation. If the patient is considered eligible by the Investigator, the patient will attend the Baseline visit (Visit 1, Day 0). At the Baseline visit, the patient will undergo the study-specific evaluations listed in Section 4.3 and will be randomized in a 1:1 ratio to either treatment with paricalcitol or no treatment based on a computer-based allocation sequence.

After the Baseline visit has been completed, the patient will be asked to return to the clinic for the Follow-up visits in the study. The initial Follow-up visits will be the Initial Safety Follow-up visits held every two weeks after the Baseline visit up to Week 6. During these visits to the clinic, blood samples will be taken from the patient for laboratory evaluations and new or changes to pre-existing adverse events will be recorded. After Week 6 up to the final Follow-up visit held at Week 48, the patients will be followed up as per standard clinical practice.

At Week 48 of the study, the patient will return to the clinic for the final Final Follow-up visit (Visit 12, Week 48). This visit will evaluate both efficacy and safety parameters, further listed and described in Section 4.3/Section and Section 4.2, respectively. Every effort will be made in order to follow-up and complete patient evaluation at these Follow-up visits. Patients who are withdrawn for any reason will also be evaluated according to the evaluation flow-chart if possible.

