### Randomisation

After review and confirmation that all study eligibility criteria have been met, the Investigator will assign a randomisation number to the subject on the Baseline Visit.

Additional information on the randomization procedure is available in Section 5.4.

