## Methods for Assigning Patients to Treatment

All patients signing the ICF and who enter the formal screening processwill be assigned a unique screening number.

Following successful completion of the screening/baseline evaluations and confirmation that the patient is eligible for participation, the patient will be randomised to treatment or not. This will be performed by the Investigator assigning a randomization number to the patient

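### The complete randomisation list is filed at the study site, where the investigator who judges eligibility also assigns the number, so upcoming allocations can be known before a patient is entered

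*Protocol*

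**What the plan says.** Four parts of the protocol bear on allocation.

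- **Generation.** In the *Randomisation* section of the statistical chapter: "The randomisation scheme (in a 1.1 ratio) will be generated by CRO using a computerised procedure". *Overall Study Design* says that patients are "randomized in a 1:1 ratio to either treatment with paricalcitol or no treatment based on a computer-based allocation sequence".
- **Custody.** The same statistical section describes the document concerned as "A complete randomisation list containing details of all patient numbers and study group". On where this document is kept, the section says that it "will be stored as essential documentation in the Trial Master File and at the study site (open study").
- **Assignment.** *Methods for Assigning Patients to Treatment* says of the randomisation step: "This will be performed by the Investigator assigning a randomization number to the patient". The *Randomisation* paragraph under *Assessments and Procedures* agrees: once eligibility is confirmed, "the Investigator will assign a randomisation number to the subject on the Baseline Visit".
- **Eligibility.** *Overall Study Design* gives this judgement to the same role: "If the patient is considered eligible by the Investigator, the patient will attend the Baseline visit (Visit 1, Day 0"). *Review of inclusion/exclusion criteria* has eligibility reviewed at Screening and again at Baseline.

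The trial is unblinded: "The study is to be performed as a randomized open intervention study". *Study Design* in the statistical chapter gives limiting bias in assignment as a reason for randomising.

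**The concern.** Randomisation protects a comparison only if whoever decides to enter a patient cannot know the next arm. Here the key from number to arm is kept where patients are enrolled, and one role both decides on entry and hands out the number. The parenthesis about the open study appears to be the whole justification. But open treatment concerns what is known after assignment, whereas concealment concerns what is known before it. An unblinded trial can keep concealment and, having no placebo, depends on it more.

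An investigator who saw the next arm could delay, decline or never approach a patient. The protocol leaves room for this. Eligibility is first assessed at a loosely defined time, around four weeks after transplantation, and is reviewed again at the visit where the number is given. Two entry criteria, eGFR and serum calcium, are laboratory values that can move between visits. With 70 patients, a few such decisions could shift the arms. Analysis can adjust only for what was measured and included in the model.

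**Working it through.** **Textual check.** The protocol states no figure on this point, so there is none to reproduce. The question is whether any provision stops the enrolling investigator from knowing the next arm.

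1. *What the list contains.* It is complete and links number to group. I take its patient numbers to be the randomisation numbers, or to map onto them; the protocol does not say.
2. *Where it is.* In the Trial Master File and at the study site.
3. *Who may open it, and from when.* Not stated.
4. *Who assigns the number.* The investigator, at Baseline.
5. *Who decides on entry.* The investigator, at Screening and at Baseline.
6. *Is there a barrier between 2 and 4?* No section describes central release, envelopes, restricted access or filing only after enrolment closes.

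The written procedure therefore permits foreknowledge. Custody of the list is a matter of trial conduct that the protocol itself settles. An analysis plan could not restore concealment once the list was in use at the site.

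**Illustration of size (assumptions).** Inputs from *Study Design* in the statistical chapter: 70 randomised, so about 35 per arm at 1:1; baseline SD 10 mg/mmol (printed with a plus sign, read as plus/minus); target difference 5.2 mg/mmol; correlation between start and end values 0.5. Assumed here: equal SDs at both times, and three patients per arm steered, each 1 SD (10 mg/mmol) low in the paricalcitol arm and 1 SD high in the control arm.

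- Baseline imbalance, control minus paricalcitol: 3/35 × (10 + 10) = 1.71 mg/mmol.
- Unadjusted final value: 0.5 × 1.71 = 0.86 mg/mmol in favour of paricalcitol; 0.86/5.2 = 16% of the target.
- Change from baseline: 0.86 − 1.71 = −0.86 mg/mmol (from unrounded values). The control arm falls further, so the bias runs against paricalcitol.
- Baseline-adjusted: 0.86 − 0.5 × 1.71 = 0 in expectation.

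**Selection on other prognostic features.** Suppose steering shifts the final value itself by δ and the analysis does not adjust. With SE = 10 × √(2/35) = 2.39, the two-sided 5% type I error becomes 1 − Φ(1.96 − δ/SE) + Φ(−1.96 − δ/SE):

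| δ (mg/mmol) | δ in SD | Type I error |
|---|---|---|
| 0.86 | 0.086 | 6.5% |
| 1 | 0.1 | 7% |
| 2 | 0.2 | 13% |
| 3 | 0.3 | 24% |

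The first row is the steering example above. The others are assumed shifts that nothing in the protocol fixes.

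**The case against.** The best defence is that the protocol shows an opportunity, not a practice. The list is stored as an essential document, and *Essential Documents* says such papers belong to the time before, during or after the study, so the date of filing is open. The parenthesis may mean only that no code-break protection is needed. An investigator who assigns a number after confirming eligibility could equally be opening a sealed envelope; neither assignment section says that the list is consulted.

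This limits what can be claimed. A reader might infer that the next allocation is known, or fully predictable. The text does not go that far, because it gives no timing and no access rule. Nor does it establish that there is one undivided sequence: blocking and stratification are not described, and *Recruitment and Screening* refers to several participating wards. For the same reason no fixed figure can be given for how guessable a concealed allocation would have been.

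There are also partial safeguards. Everyone who signs consent goes on a screening log and receives a screening number, enrolled patients go on an enrolment log, and eligibility is checked twice. Skipping a consented patient would leave a trace. But the logs do not prevent delay, and they miss patients who were never approached, so they do not replace concealment.

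Finally, the baseline urine sample is scheduled for the randomisation visit, so the investigator may not have the study albumin/creatinine result when allocating. That weakens the steering example but not the point about custody of the list.

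**Conclusion.** The point stands as a design fault in the written procedure. The protocol places the full list at the site without restriction and gives assignment to the person who decides on entry, so upcoming allocations can be known and selection bias is not prevented. This works against the protocol's own reason for randomising. The open design does not excuse it.

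No size of bias follows from the documents, and none is needed for the conclusion. A reader might set the 1.71 mg/mmol imbalance against the 5.2 mg/mmol target and infer a bias of a third of the effect. That compares a baseline shift with a treatment effect. At the protocol's own correlation, with equal SDs assumed, 16% carries to an unadjusted final value, the direction reverses for a change score, and adjustment removes it in expectation. Adjustment cannot remove selection on prognosis that was not measured. The correction needs to be in place before patients are enrolled, since lost concealment cannot be restored afterwards.

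**What to change.** Amend the statistical chapter's *Randomisation* section to state that:

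- the unit that generates the list holds it, with access restricted to named functions not involved in enrolment, and any Trial Master File copy is under the same restriction;
- each allocation is released singly, only after consent, confirmed eligibility and irrevocable registration of the patient, by web, by telephone or by sequentially numbered opaque sealed envelopes;
- the full list is filed at the site only after the last patient has been randomised.

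Then align *Methods for Assigning Patients to Treatment* and the *Randomisation* paragraph under *Assessments and Procedures*, so that the investigator requests and records an allocation rather than assigning a number. Site filing need not be barred altogether; delaying it until enrolment closes is enough.

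Treatment stays open and the sample size is unaffected. The cost is the wording change plus one call, web entry or envelope per patient, for about 70 patients.

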## Statistical Analysis Plan

The main hypothesis:

In renal transplant recipients’ treatment with paricalcitol is superior to placebo, and results in reduced albuminuria at 12 months treatment.

## Study Populations

Intention-to-treat population:

The ITT population will consist of all randomized patients who received at least one dose of active medication or placebo therapy after Visit 1 and have at least one post-baseline assessment of the primary efficacy variable (proteinuria). Randomized patients without data on the primary outcome variable will be excluded from this population.

The ITT population will be analyzed following the intent to treat principle.

Per protocol population:

The Per-protocol Population will consist of all ITT patients who did not show major deviations from the protocol procedures that may have an impact on the study outcome and who have completed the treatment phase at 12 months according to protocol. Criteria that are assumed to have such an impact will be defined before analysis during the Blind Review Meeting.

Safety population:

The Safety Population (SAF population) will consist of all patients in whom transplantation was performed and who were randomized and treated with at least one dose of randomized treatment

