#### Clinical laboratory tests - urine

Proteinuria will be evaluated with a spot urine for albumin/creatinine. Spot urine will be measured according to standard methods. Urine samples for evaluation of proteinuria will be taken at Baseline and at the Final Safety Follow-up visit.

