# STUDY MEDICATION

## Study Medication and Comparator

Patients are randomized into two arms. Paricalcitol will be prescribed for the active arm.

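### The analysis populations require a dose, but controls are untreated, so as written no control qualifies; the ITT set also drops randomised patients who lack the outcome

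*Protocol*

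**What the plan says.** **Design.** Under Overall Study Design, patients are "randomized in a 1:1 ratio to either treatment with paricalcitol or no treatment". Study Medication and Comparator adds: "Patients are randomized into two arms. Paricalcitol will be prescribed for the active arm". The Study Design and Randomisation sections of the statistical chapter both call the trial open, and no placebo is described in any procedure.

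**Hypothesis.** The section headed Statistical Analysis Plan states that "treatment with paricalcitol is superior to placebo".

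**Populations** (Study Populations):
- ITT consists of "all randomized patients who received at least one dose of active medication or placebo therapy after Visit 1" who also have a post-baseline value of the primary variable. The rule continues: "Randomized patients without data on the primary outcome variable will be excluded from this population". The next line says that this set is analysed by intention to treat.
- Per-protocol is a subset of ITT.
- Safety consists of transplanted patients "who were randomized and treated with at least one dose of randomized treatment".

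**Timing of the primary variable.** "Urine samples for evaluation of proteinuria will be taken at Baseline and at the Final Safety Follow-up visit". The Proteinuria section and the albumin/creatinine row of the flow chart agree: baseline, then week 48 or month 12.

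**The concern.** Two rules decide who is analysed, and neither fits this trial.

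The first is the dose condition. It presupposes that both arms receive something, and here only one does. A rule that one whole arm cannot meet leaves the primary and safety comparisons without a defined control group. Someone must then supply an unwritten rule, in a trial where allocation is known to everyone.

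The second is the outcome condition. Leaving out randomised patients because their outcome is missing is a selection made after randomisation. If the reasons for missingness differ between arms, the comparison is no longer protected by the randomisation, although the set is labelled ITT.

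The placebo wording of the hypothesis adds a third problem. A conclusion of superiority to placebo could not be drawn from an open comparison with no treatment.

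**Working it through.** **Step 1. Arm sizes.** Estimation of Sample Size gives 30 per arm and a total of 70 randomised. At 1:1 that is 70 / 2 = 35 per arm.

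The 30 can be reproduced from the stated inputs: difference 5.2, SD 10 (the printed 15.0 + 10 is read as plus or minus one SD), correlation 0.5, type I error 5% (taken as two-sided), power 80%.
- SD of change = 10 × √(2 × (1 − 0.5)) = 10.
- n = (10 × (1.960 + 0.842) / 5.2)² = 29.03, rounded up to 30.

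This is a one-sample (within-arm) formula, which is a separate matter. The present point uses only the arm sizes.

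**Step 2. Apply the dose conditions as written to 35 + 35.**

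| Set | Dose condition | Paricalcitol | Control |
|---|---|---|---|
| ITT | active drug or placebo | at most 35 | 0 |
| Per-protocol | inherited from ITT | at most 35 | 0 |
| Safety | allocated treatment | at most 35 | 0 |

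Only the ITT rule names placebo. The safety rule reaches the same result because an arm allocated to no treatment has no dose to take. Other safety wording is also tied to dosing: adverse-event collection ends 7 days after the last dose (Safety evaluation methods), which has no counterpart for a control.

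**Step 3. Suppose controls are kept anyway.** The dose condition then acts on one arm only. It can remove a paricalcitol patient who never took a capsule but has no way to remove a control. Study drug is given or dispensed at the baseline visit (Visit 1 schedule and flow chart), so few such patients are likely.

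**Step 4. Apply the outcome condition.** Only one post-baseline ratio is scheduled, at week 48 or month 12. A patient therefore enters ITT by having that value. Under Patient Withdrawal:
- patients who stop drug but continue visits remain in efficacy follow-up, so those who attend week 48 stay in ITT;
- a final evaluation is required at withdrawal, which might supply an earlier value, but its visit number is blank and no ratio is scheduled for it.

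The protocol gives no dropout rate. With an assumed proportion lacking the value, equal in both arms and with the dose clause repaired, the set is 70 × (1 − proportion):

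| Assumed proportion without a value | Patients in ITT |
|---|---|
| 0% | 70 |
| 5% | 66.5 |
| 10% | 63 |
| 15% | 59.5 |
| 20% | 56 |

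**Step 5. Can bias be sized?** In one arm, the mean among observed patients differs from the full-arm mean by (proportion missing) × (mean of those observed minus mean of those missing). The bias in the treatment comparison is the difference between the arms in that product. The protocol gives neither the proportions nor the gaps, so the bias cannot be computed.

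**The case against.** The best defence is that the placebo wording is leftover text. Every design section makes the comparison plain, and no analyst would discard the control arm. That is probably right about what would happen. It does not supply the missing rule, and it confirms that the written one cannot be applied.

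Some may say that requiring an outcome value is common and that missing data belong in a statistical analysis plan that is not shown. The method for missing values can indeed be left there. The exclusion itself, however, is fixed in the protocol, next to a statement that intention to treat is followed. Those two lines conflict whatever a later plan says.

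Stronger readings are tempting but not supported:
- **ITT equals treatment completers.** A reader might infer this from the single post-baseline measurement. Patient Withdrawal contradicts it: stopping drug for adverse events, on request or for intercurrent illness leads to continued efficacy visits. Completing treatment is a condition of the per-protocol set.
- **Losses from hypercalcaemia will bias the result.** The protocol's stated response to hypercalcaemia is dose reduction, and stopping drug for adverse events does not end follow-up. The reasons listed for complete withdrawal are the patient's decision and loss to follow-up.
- **The planned blind review for per-protocol deviations is impossible in an open trial.** Deviations can be classified with arm labels removed, so impossibility is not shown.

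**Conclusion.** The population definitions and the stated comparator are wrong as written and should be corrected before any analysis. The literal effect is 0 of about 35 controls in the ITT, per-protocol and safety sets. A reader might infer that the control arm will really be lost; the design sections make that unlikely. The practical defect is that control membership rests on an unwritten rule and that the surviving dose condition works against one arm only, probably for few patients.

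Separately, the set called ITT consists of patients with a final albumin/creatinine ratio, apart from any value obtained at withdrawal. This conflicts with the principle that the same section claims.

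No bias figure can be attached. A reader might treat the gap between 60 needed and 70 randomised as a planned loss of 10 / 70 = 14%, and assume that lost paricalcitol patients have ratios 10 mg/mmol worse, with no loss among controls. That gives 0.14 × 10 = 1.4 mg/mmol, or 27% of 5.2. The protocol states no dropout rate, the 10 mg/mmol has no source and equals a full SD on its own figures, and similar losses among controls would offset the effect. The conclusion here does not use that figure. It rests only on the protocol's wording and schedule.

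**What to change.** Reword the hypothesis and the population definitions:

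1. **ITT:** all randomised patients, analysed in the arm assigned, whether or not any dose was taken. Delete the exclusion for missing outcome data. Handle missing week-48 values in the analysis, with a sensitivity analysis. Because only one post-baseline ratio is scheduled, a patient without it adds little direct information, so the sensitivity analysis carries much of the weight.
2. **Safety:** all randomised patients by treatment actually received, that is, paricalcitol if at least one dose was taken and otherwise none, with controls counted from randomisation.
3. **Hypothesis:** superiority over no paricalcitol treatment, stated as open label.

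The per-protocol set, being drawn from ITT, then no longer inherits the dose condition.

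The cost is a text amendment and some added analysis work for missing values. No new visits, samples or patients are needed. Measuring the ratio at interim visits would be a redesign and is not part of this correction. The flow chart shows urine tests at every visit, but the urine section schedules proteinuria samples only at baseline and the final visit, and the Week 2, 4 and 6 visit list contains no urine sample.
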